**Brief Summary**

This is a Canadian, multi-centre, double-blind randomized controlled trial of an **innovative** vaginal surgery technique for correction of pelvic organ prolapse (POP) in women. Vaginal surgery is preferred as minimally invasive, however we do not know if materials such as synthetic polypropylene mesh improve success, durability and cost-effectiveness. Our principal goal is to compare our experimental bilateral sacrospinous vaginal vault fixation with **synthetic mesh arms (BSSVF-M)** to the current standard of sacrospinous ligament suspension with **synthetic sutures (SSLS)** over a timeline of 2 years. Patients and evaluators will be blind to technique.

**Trial Registration**

ClinicalTrials.gov

**Funding** CIHR 2016-2021

**Introduction**

**Background and Rationale**

The pelvic floor comprises muscles, nerves and a fascial network with dynamic, elastic ligaments of support. Pelvic organ prolapse (POP) occurs when the capacity to accommodate pressure and stretch is exceeded and increases with childbirth and aging.^1^ One in five women need surgery for POP.^2^ POP suspension performed vaginally is among the most important ideas in gynecology in the past few decades, however we do not know which technique is best. The nominated principal applicant (NPA) has developed a novel surgery: bilateral sacrospinous vaginal vault fixation with synthetic mesh arms (BSSVF-M), which may be more successful, durable and cost-effective than standard sacrospinous ligament suspension with sutures (SSLS) and may thus become the preferred vaginal POP surgery both nationally and internationally. A Cochrane review on surgical management of POP concluded that *“adequately powered RCTs with blinding of assessors are urgently needed […] they particularly need to include women's perceptions.”*^3^ The OPTIMAL trial, a large RCT comparing 2 POP surgeries, established a stringent definition of success using a composite outcome of objectively measured POP, subjective improvement and the need for another treatment for POP recurrence.^4^

Identifying the best way to surgically suspend the vagina for POP can make the difference between a woman who can enjoy a desired level of physical activity at work or play, empty her bowel and bladder without concerns, engage in a normal sexual life and a woman who can’t perform these basic activities without discomfort, pain, worry and shame.^5-8^ The vaginal approach for pelvic surgery offers less pain, a shorter hospital stay, a faster recovery and no external incisions.^3^ However, **what is the safest, most durable, most cost-effective vaginal POP surgery?** Prior operations have produced unacceptable complications or a need for reoperation for POP recurrence.^9^ Further suffering for women and unacceptable healthcare costs ensued. Because seniors (over age 65) are the fastest growing age group in Canada, the CIHR states research into aging should be prioritized.^10^ By 2031, Statistics Canada estimates the number of senior women to reach 5.1 million or 24% of the total female population.^11^ Women have longer life expectancy than men.^11^ The burden of POP increases with age; 1 of 2 women over 80 experience pelvic floor dysfunction.^1^ For some aging women, vaginal surgery is the only option because of comorbidities precluding more invasive or lengthier open abdominal surgeries.^9^ Currently, there is true clinical equipoise between BSSVF-M and SSLS. **Our novel mesh insertion technique, BSSVF-M, offers the advantages of small size, deep, tension-free and tailored to individual anatomy**. This ensures midline restoration of the vaginal axis^12^ and maintains flexibility for normal bladder, bowel and sexual function.^13^ Tension-free insertion of BSSVF-M is a key difference with SSLS, which pulls the vagina tight against ligaments, causing pain or the return of POP after SSLS. Surgical innovation is important but adoption of new procedures needs reliable evidence acquired through a rigorous **I**nnovation, **D**evelopment, **E**xploration, **A**ssessment, **L**ong-term study (IDEAL) paradigm.^14^

We have been studying BSSVF-M over the past 9 years. Initial development included a magnetic resonance imaging study establishing restoration of pelvic anatomy comparable to normal.^12^ An exploratory prospective cohort study followed, showing BSSVF-M to be safe, easily taught to other surgeons and successful in 77% of women at one year, with the OPTIMAL composite outcome.^13^ This is superior to the reported 60% success of the SSLS^13^ and informed our power calculation for the proposed RCT. An informal survey of 50 Western Society for Pelvic Medicine surgeons indicated that an average of 14% increase in composite outcome success would be sufficient to adopt a new vaginal suspension technique. We are now at the IDEAL^14^ assessment stage, where our novel technique warrants an RCT before widespread adoption. The results of this trial will directly inform surgeons whether mesh should be used for vaginal repair of POP and how to counsel patients. This trial includes knowledge translation for women to understand pelvic floor symptoms, related condition-specific quality of life, sexual health and body image after two vaginal surgery procedures. A rigorous cost effectiveness analysis will inform different stakeholders and policy makers regarding cost effectiveness.

**Primary Objective**

To compare BSSVF-M *vs.* SSLS via the OPTIMAL composite outcome measure at 2 years.

**Secondary Objectives**

To determine condition-specific urinary, bowel and POP symptoms, quality of life, new onset pelvic pain, gender-specific body image, sexuality, global improvement, adverse events, reoperations and health utility up to 2 years post BSSVF-M *vs.* SSLS. Validated questionnaires and adverse event schemes will be used. A Markov model will estimate 10-year health benefits and costs of surgery.

**Methods (fig 1)**

**Study Setting**

Tertiary care urogynecology centres in Vancouver, Edmonton, Montreal, Hamilton

**Eligibility**

Inclusion Criteria

- Women over 19 years of age
- Able to read and write in English, or alternatively have someone to translate for them
- Able to follow up with clinic visits for up to two years after surgery
- Diagnosed with bothersome pelvic organ prolapse including at the top of the vagina

Exclusion Criteria

- Women who wish to conserve the uterus
- Prior pelvic radiation
- Prior vaginal mesh surgery for prolapse
- Prior vaginal mesh exposure
- Presence of vaginal pain from pelvic floor muscle spasm documented at baseline visit
- Plan for synthetic vaginal mesh insertion for prolapse, at the same time, at locations other than the top of the vagina (NOTE: concurrent need for synthetic anti-incontinence sling is NOT an exclusion)
- Immune compromise; chronic steroid use
- Current smoker
- Currently pregnant or breastfeeding
- Presence of pain syndromes likely to cause a heightened sensitivity to pelvic pain (example: fibromyalgia or painful bladder syndrome)

**Interventions (fig 2):**

Patients > age 19, symptomatic POP (stage 1-4^15^) randomized to BSSVF-M or SSLS. Both surgeries are performed through the same vaginal incisions. BSSVF-M uses bilateral synthetic polypropylene mesh arms for support of the vaginal wall and SSLS uses two synthetic sutures attached uni- or bilaterally.^3,16^ As both are performed through the same incision, women will not know their treatment. Group assignment will remain blinded through trial end. Surgeons will receive group allocation immediately prior to surgery. To diminish bias, research personnel conducting pelvic exams to evaluate the primary outcome will be blind to the type of procedure.

**Outcome measures**

Primary, at 2 yrs

Composite outcome of 3 objective signs and 1 subjective symptom of POP (yes/no answers). The definition of surgical success, used in the OPTIMAL trial^4^ is the absence of all of the following: (1) objectively recorded, via POP quantification (POP-Q)^15^, recurrent POP of the top of the vagina beyond the upper third of the vaginal canal; (2) objectively recorded, via POPQ, recurrent POP of the anterior or posterior vaginal walls beyond the hymenal ring (vaginal entrance); (3) vaginal bulge symptoms reported by the patient, as indicated by an affirmative response to either: *“Do you usually have a bulge or something falling out that you can see or feel in the vaginal area?”* and any response other than *“not at all”* to the question *“How much does that bother you?”* (4) re-treatment for prolapse by either surgery or pessary (conservative treatment with insertion of a silicone ring in the vagina for support). The POPQ is a validated quantification system with adequate interrater reliability which measures, in centimeters, the extent of vaginal wall descent with respect to a reference point at the hymenal ring.^15^

Secondary, at 6 weeks, 6, 12 and 24 months

Change in maximal POP of vaginal compartments via POPQ, obtained by research personnel (nurse or clinical fellow) trained in POPQ and blinded to group allocation. POP will be quantified and compared to baseline. Numerical questionnaire scores will be compared between the two groups from baseline to 6 weeks, 12 and 24 months postoperatively. Change in questionnaire scores between the 2 groups from baseline to 6 weeks, 12 and 24 months postoperatively: Pelvic Floor Distress Inventory (PFDI-20) and the Pelvic Floor Impact Questionnaire (PFIQ-7)^17^; the short form McGill pain questionnaire^18^; a validated gender-specific body image scale specifically for POP.^8^ Change in questionnaire scores between the 2 groups from baseline to 12 and 24 months: Pelvic organ prolapse/ Incontinence Sexual Questionnaire, IUGA-Revised (PISQ-IR)^19^. Difference between global impression of improvement (Likert Scale) of the 2 groups at 6 weeks, 12 and 24 months postoperatively. Difference between the 2 groups in length of surgery, postoperative hospital stay, complications such as pain or mesh exposure, reoperations and other unexpected adverse events categorized using the Clavien Dindo validated classification system for surgical complications.^20^ Difference in health utilities measured via the EuroQol instrument (EQ-5D)^21,22^ and in direct healthcare utilization and costs collected by the healthcare service utilization questionnaire^23^ at baseline, 6 weeks, 6, 12 and 24 months postoperatively.

Health economic evaluation

A cost-effectiveness analysis (CEA) of BSSVF-M *vs*. SSLS will be conducted alongside the 2-year trial from the healthcare system perspective. The incremental cost-effectiveness ratio (ICER) during the 2-year study period will be calculated by dividing the difference in 2-year costs by the difference in the Quality Adjusted Life Years (QALYs). Bootstrap method will estimate the uncertainty surrounding ICER. In addition, an alternative CEA will be carried out over 10 years after commencement of surgical treatment by a Markov model. Published Markov models^24,25^ will be adapted to simulate transition between different health states postoperatively and to extrapolate within-trial results over 10 years. Specifically, the potential health states include repaired POP without late/post-operative complications, repaired POP with minor late complications, and repaired POP with major late complications requiring revision surgery. All costs and QALYs will be discounted at a rate of 3% per year. The ICER will be estimated. Probabilistic sensitivity analysis with 1000 Monte-Carlo simulations will be employed to assess the impact of model parameters with greater uncertainty and calculate the 95% credible interval of the ICER.

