**Sample size**

179 women/group (358 total). Our Western Canadian survey of 50 surgeons indicated the smallest clinically relevant difference to change surgical practice would be an absolute change of 14%. The proportion of success in the control SSLS group was 60.5% in the OPTIMAL trial^4^ and the success rate with BSSVF-M was 77% in our one-year pilot study.^13^ Our pilot study was small and designed to inform a power calculation for an RCT; it did not study long-term results, cost effectiveness or KT strategies. Studies of mesh vs sutures in surgery for urinary incontinence indicate that mesh is more successful, durable and cost-effective than sutures,^26-29^ therefore we expect similar results for POP, with sustained durability of mesh over time. Our primary analytic strategy, following the example of the OPTIMAL trial, will include only patients who come for 2-yr follow-up or who were failures on the last follow-up. Patients who do not come to their 2-yr follow-up but who were failures at last follow-up will be counted as failures. Sample size was determined based on a two-sample test of independent proportions, using two-sided ∝=0.05, anticipated successful outcome rates 60 and 75%, power=80% and yielded 152 patients/group. To account for an estimated 15% loss to follow-up (patients who never had a follow-up visit or who were deemed successful on their last follow-up), similar to the OPTIMAL trial, our sample size was increased to 179 per group.

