| Questionnaires:  Self-reported Charlson Comorbidity Index  Pelvic Floor Distress Inventory – 20 (PFDI-20)  Pelvic Floor Impact Questionnaire – 7 (PFIQ-7)  Pelvic organ prolapse/Incontinence Sexual Questionnaire (PISQ-IR)  The short form McGill Pain Questionnaire (McGill PQ)  The Body Image in Pelvic Organ Prolapse Questionnaire (BIPOP)  EQ-5D-3L Questionnaire (within the last 6 months)  Healthcare service utilization questionnaire (within the last 6 months) | | | | |
| OR details | | **INTRAOP** | | OR details |
| 6 week POP Quantification  Clavien Dindo complication scale | | **POSTOP** | | 6 week POP Quantification  Clavien Dindo complication scale |
| Questionnaires:  PFDI-20  PFIQ-7  McGill PQ  BIPOP  Global Question of Improvement  EQ-5D-3L  Healthcare service utilization questionnaire | | | | |
| 6 month phone call | | **PHONE EVALUATION** | | 6 month phone call |
| Questionnaires:  EQ-5D-3L  Health care service utilization questionnaire | | | | |
| 12 month questionnaires  POP Quantification  Clavien Dindo complication scale | | **MID-TRIAL ASSESSMENT** | | 12 month questionnaires  POP Quantification  Clavien Dindo complication scale |
| Questionnaires:  PFDI-20  PFIQ-7  PISQ-IR  McGill PQ  BIPOP  Global Question of Improvement  EQ-5D-3L  Healthcare service utilization questionnaire | | | | |
| 24 month questionnaires  POP Quantification  Clavien Dindo complication scale | | **FINAL ASSESSMENT** | | 24 month questionnaires  POP Quantification  Clavien Dindo complication scale |
| Questionnaires:  PFDI-20  PFIQ-7  PISQ-IR  McGill PQ  BIPOP  Global Question of Improvement  EQ-5D-3L  Healthcare service utilization questionnaire | | | | |

**Figure 2:** **Vault suspension techniques:** a) **BSSVF-M**^13^ – novel technique performed with bilateral synthetic mesh arms attached to sacrospinous ligaments to replace the vagina tension-free in its normal anatomic orientation within the pelvis, can carry risks of mesh exposure and pain; b) **SSLS** - standard technique mostly performed with unilateral (but can be bilateral) synthetic sutures attached to sacrospinous ligaments, tensioned and anatomically incorrect, can carry risks of pain, detachment and prolapse recurrence.

[figure not shown]

[figure not shown]

1. Bilateral Sacrospinous Vault Fixation b) Unilateral Sacrospinous Ligament

with **Mesh arms (BSSVF-M)^13^** Suspension with **synthetic sutures (SSLS)**

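### The 10-year model's uncertainty output is fixed as a 95% credible interval of the ICER, which cannot be interpreted if draws of the QALY difference fall on both sides of zero

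*Protocol*

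**What the plan says.** The protocol (Outcome measures, Health economic evaluation) defines the 2-year ICER as the between-group cost difference divided by the between-group QALY difference. Two sentences then deal with its uncertainty.

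- **Within-trial, 2 years:** "Bootstrap method will estimate the uncertainty surrounding ICER". No interval type and no other output is named.
- **10-year Markov model:** 1000 Monte Carlo simulations will be "employed to assess the impact of model parameters with greater uncertainty and calculate the 95% credible interval of the ICER". Here the output is named.

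The protocol mentions no net monetary benefit, cost-effectiveness plane, acceptability curve or willingness-to-pay value. It gives no expected QALY difference, cost difference or standard deviation for either.

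Two other places bear on the likely sign of the QALY difference. Background and Rationale states "Currently, there is true clinical equipoise between BSSVF-M and SSLS". The legend to Figure 2 says that the mesh procedure "can carry risks of mesh exposure and pain".

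**The concern.** An ICER has a consistent meaning only while its denominator keeps one sign. Write ΔC for the cost difference and ΔQ for the QALY difference, mesh minus suture. When ΔQ > 0, an ICER below a threshold λ means that mesh is worth its cost at λ. When ΔQ < 0, the inequality reverses. A negative ratio can then mean dominant (cheaper, better) or dominated (dearer, worse). A positive ratio can mean paying more for a gain or saving money at a loss of health. Sorting such draws and cutting at the 2.5th and 97.5th percentiles ranks values that do not lie on one scale.

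The Introduction promises a cost-effectiveness analysis for stakeholders and policy makers. If the draws straddle zero, the interval that the plan commits to would not tell them whether mesh is good value or how sure to be of it.

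**Working it through.** **1. The number per arm.** The only relevant figures in the protocol are those under Sample size: "anticipated successful outcome rates 60 and 75%, power=80% and yielded 152 patients/group", with two-sided alpha 0.05. The two-proportion formula without continuity correction is

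n = [1.960·√(2·0.675·0.325) + 0.842·√(0.60·0.40 + 0.75·0.25)]² / 0.15² = 151.9, so 152.

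Allowing for 15% loss, 152/0.85 = 178.8, so 179. Both stated figures reproduce. I use 152 per arm below, assuming that the economic data are as complete as the primary outcome.

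**2. Why the ratio fails as a scale.** Take ΔC = ±500 and ΔQ = ±0.02 (assumed) and compare the ratio with net monetary benefit, NMB = λ·ΔQ − ΔC, at an assumed λ = 50,000.

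| ΔC | ΔQ | ICER | NMB |
|---|---|---|---|
| −500 | +0.02 | −25,000 | +1,500 |
| +500 | −0.02 | −25,000 | −1,500 |
| +500 | +0.02 | +25,000 | +500 |
| −500 | −0.02 | +25,000 | −500 |

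Each ICER value arises from two opposite conclusions. NMB separates them.

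**3. How often the denominator could change sign within the trial.** SE(ΔQ) = SD·√(2/152) = 0.1147·SD, and P(estimated ΔQ < 0) = Φ(−ΔQ/SE). The differences and SDs of 2-year QALYs are assumptions.

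| True ΔQ | SD 0.20 | SD 0.30 | SD 0.40 |
|---|---|---|---|
| 0 | 50% | 50% | 50% |
| 0.02 | 19% | 28% | 33% |
| 0.05 | 1.5% | 7% | 14% |
| 0.10 | <0.1% | 0.2% | 1.5% |

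For example, with ΔQ = 0.02 and SD = 0.30, SE = 0.0344 and Φ(−0.58) = 28%.

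**4. Which row the design points to.** Suppose that all QALY gain came through surgical success and that the planned 15-point difference held for the full two years. Then ΔQ = 0.15 × 2 × (utility gap between success and failure). Assumed gaps of 0.05, 0.10 and 0.20 give 0.015, 0.03 and 0.06. A ΔQ of 0.10 would need a gap of 0.10/0.30 = 0.33 from the day of surgery. Under this assumption the lower differences are the more natural ones. It is not a forecast.

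**5. What the two summaries look like.** A bootstrap with 5000 resamples used 152 per arm, QALY SD 0.3, cost SD 4000, ΔC = +500 and λ = 50,000, all assumed.

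- **ΔQ = 0.02:** the ICER is 25,000, with percentile limits of about −190,000 to +209,000. Shares of resamples: dearer and better 62%, dearer and worse 24%, cheaper and better 10%, cheaper and worse 4%. From the same resamples, incremental NMB has median 483, 95% interval about −2,975 to 3,868, and probability cost-effective 0.61.
- **ΔQ = 0.15:** no resample has ΔQ ≤ 0. The ICER limits are about −2,700 to 11,100, and the negative limit can be read as dominance. The incremental NMB interval is about 3,800 to 10,300.

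The ratio interval fails in the first case and is usable in the second. The NMB interval works in both.

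**The case against.** The strongest reply has four parts.

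- **The bootstrap sentence fixes no interval.** This stands. Bootstrapping paired cost and QALY differences is standard and serves a plane, an acceptability curve or net benefit equally well. A reader might infer that the 2-year ratios will be ranked and cut at percentiles; the text does not say so.
- **Reporting detail may sit in an analysis plan not shown here.** This stands for the absence of net benefit, thresholds and curves, which is no fault in itself. It does not cover the credible interval of the ICER, which the protocol names as an output and which a plan that follows it would have to produce. The protocol does not call it the only output, however.
- **The arithmetic above is not for the 10-year model.** This also stands. Steps 3 and 5 use trial sampling error. The model's draws come from parameter distributions and 10 years of accrued QALYs, and their spread could be smaller or larger. A reader might carry the 1.5% to 28% over to the model; the document gives no basis for that.
- **The trigger is assumed.** No QALY difference or SD is stated. Equipoise and the risks of mesh exposure and pain make a near-zero or negative difference possible, not established. A reader might conclude that the interval is certain to be meaningless or to miss the true ratio. That does not follow: with a clear QALY gain it is usable, and no coverage was computed.

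**Conclusion.** The point holds in a limited, conditional form. For the 10-year model the protocol commits to a summary that loses its meaning if draws of the QALY difference fall on both sides of zero, and nothing in the protocol rules that out. For the 2-year analysis it makes the ratio the target of the bootstrap but leaves the form of the result open, so there is an ambiguity to close rather than an error.

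The size is known only by within-trial illustration, on assumed inputs and 152 per arm. For QALY differences of 0.02 to 0.05 and SDs of 0.20 to 0.30, the chance of a negative estimate runs from about 1.5% to 28%. At a difference of 0.10 it is 1.5% or less for SDs up to 0.40. No corresponding figure can be given for the 10-year model.

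This concerns a secondary economic analysis. The primary outcome, sample size and data collection are unaffected. The change is still worth making, because the alternative is valid whichever way the QALY difference falls.

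**What to change.** In Health economic evaluation, replace the 95% credible interval of the ICER with these outputs, all from the same 1000 Monte Carlo draws:

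- incremental cost and incremental QALYs, each with a 95% interval;
- incremental net monetary benefit with a 95% interval, at willingness-to-pay values stated before the analysis;
- a cost-effectiveness plane and an acceptability curve.

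Name the same outputs for the within-trial bootstrap. In both analyses give the ICER as a point estimate only, and where one procedure dominates, say so in words instead of printing a negative ratio.

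The cost is a small amendment to the wording and some extra reporting. No new data, patients or simulations are needed. The one decision to add is the set of willingness-to-pay values, which the protocol does not now state.

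### The health states named for the 10-year Markov model are all repaired prolapse; untreated or pessary-managed recurrence has no named state, so the model as described does not carry the durability difference beyond year 2

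*Protocol*

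**What the plan says.** The Protocol plans two cost-effectiveness analyses under Outcome measures, Health economic evaluation. The first runs alongside the trial for 2 years. The second is a model: "an alternative CEA will be carried out over 10 years after commencement of surgical treatment by a Markov model". Published models "will be adapted to simulate transition between different health states postoperatively and to extrapolate within-trial results over 10 years". The only description of structure follows: "potential health states include repaired POP without late/post-operative complications, repaired POP with minor late complications, and repaired POP with major late complications", the last of these needing revision surgery. On discounting: "All costs and QALYs will be discounted at a rate of 3% per year". A probabilistic sensitivity analysis with 1000 simulations is to address uncertain parameters.

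The primary outcome, under the same main heading, counts a woman as a failure for any of four reasons. These include "recurrent POP of the top of the vagina beyond the upper third of the vaginal canal" and "re-treatment for prolapse by either surgery or pessary"; the other two are wall prolapse beyond the hymen and bothersome bulge symptoms.

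The Sample size section plans on 60% and 75% success. Arguing from incontinence surgery, it states "therefore we expect similar results for POP, with sustained durability of mesh over time". The Figure 2 legend lists recurrence among the risks of SSLS and mesh exposure among those of BSSVF-M.

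**The concern.** A 10-year model is added to a 2-year trial mainly to value what happens after follow-up ends. Here that is durability: whether the repair holds longer with mesh arms than with sutures. Yet the named states sort women by complications of a repair and never by whether the prolapse has come back.

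The gap is uneven. Mesh exposure, which the Challenges/Mitigation section says may need surgery, fits the listed states. A woman with recurrent prolapse who is untreated or uses a pessary does not. A model built on these states would count the complications of both procedures and leave out much of the cost and quality-of-life loss from recurrence. The resulting ICER would be unfavourable to whichever procedure is more durable; if the protocol's own expectation is right, that is BSSVF-M. The Secondary Objectives include the 10-year estimate, and the Background says the economic results are meant to inform policy makers.

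**Working it through.** **1. Planning rates.** The protocol gives no numerical result for the Markov model, so there is none to reproduce. The 60% and 75% used below are confirmed by the sample size. With two-sided alpha 0.05, 80% power and pooled variance:

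n = [1.960 × √(2 × 0.675 × 0.325) + 0.842 × √(0.60 × 0.40 + 0.75 × 0.25)]² / 0.15² = 151.9, so 152 per group; 152 / 0.85 = 178.8, so 179.

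Both agree with the protocol. Planned failure is therefore 40% and 25%, a difference of 15 points. Applied to 179 women per group this is 179 × 0.40 = 71.6 and 179 × 0.25 = 44.75, or about 72 and 45 women.

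**2. Where each outcome would sit in the model as described.**

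| Outcome | Named state |
| --- | --- |
| Anatomical recurrence (apex or walls), untreated | None |
| Bothersome bulge symptoms, untreated | None |
| Recurrence managed by pessary | None |
| Recurrence treated by surgery | Possibly the third, if revision surgery is read to include it |
| Mesh exposure needing surgery | Third |
| Death | None |

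**3. Illustrative size.** The protocol gives no utility loss for recurrence, so a value of 0.05 per year (range 0.02 to 0.10) is assumed. The 15-point difference is first held constant through years 3 to 10.

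- Discounted years at 3%, counted at year end: (1 − 1.03⁻¹⁰)/0.03 − (1 − 1.03⁻²)/0.03 = 8.530 − 1.913 = 6.617.
- Difference per woman: 0.15 × 0.05 × 6.617 = 0.050 QALY.
- Range: 0.15 × 0.02 × 6.617 = 0.020 to 0.15 × 0.10 × 6.617 = 0.099.
- Counted at the start of each year, the factor is 6.617 × 1.03 = 6.815, giving 0.020, 0.051 and 0.102.

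**4. Sensitivity to failures after year 2** (assumed rates, start-of-year discounting, same utility range):

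| Later annual failure, SSLS / BSSVF-M | QALY difference per woman |
| --- | --- |
| 0% / 0% | 0.020 to 0.102 |
| 5% / 5% | 0.016 to 0.082 |
| 5% / 2.5% | 0.026 to 0.129 |

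The figure shrinks if the arms converge and grows if they separate further. Costs of re-treatment after year 2 would be additional; the protocol gives no figures from which to size them.

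**The case against.** A reader might infer that the model cannot credit durability at all, or that it treats every repair as permanently intact. The document does not support that, for three reasons.

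- The list is introduced as potential states that are included, and published models are to be adapted. It is not closed, and nothing excludes a recurrence or death state. The cited models are not at hand, so nothing can be said about their structure.
- The third state involves revision surgery. The secondary outcomes group reoperations with complications, and Figure 2 lists recurrence alongside other surgical risks. Reoperated recurrence could reasonably be placed there.
- If state utilities and costs were taken by arm from the trial's EQ-5D and resource-use data, some effect of early failures would be carried forward indirectly.

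The QALY illustration is also open to challenge. It applies the full loss to every composite failure, although the anatomical components require no symptoms, and it keeps that loss for eight years, although successful re-treatment would relieve it.

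On death, eligibility is women over 19 and no age distribution is given, so the size of that omission cannot be judged. It is a supporting point only.

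It is also fair to say that full model detail can be left to an analysis plan. But the protocol chose to name the states, and what it left out is its own primary endpoint. On any of these readings, untreated and pessary-managed recurrence has no named place. Simulating over uncertain parameters cannot restore a state that the structure lacks.

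**Conclusion.** The point holds for the model as described, not for every model the wording would permit. The named states do not represent the primary endpoint or the durability hypothesis after year 2, while they do represent complications, so the 10-year ICER would be distorted. The 2-year analysis, if based on the EQ-5D and costs collected in the trial, captures recurrence up to that time and is unaffected. So are the primary analysis and the sample size.

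The illustrative size is about 0.02 to 0.10 QALY per woman. It rests on the planning failure rates, an assumed utility loss of 0.02 to 0.10 per year, and a 15-point difference that persists to year 10. It is an upper range provided the difference does not widen, and smaller if some failures are asymptomatic or successfully re-treated. Severity is moderate.

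**What to change.** Revise the model description under Health economic evaluation to:

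- add states for recurrent or failed prolapse (untreated, pessary, reoperated), a post-reoperation state, and death;
- keep revision surgery for a complication separate from reoperation for recurrence, or state explicitly that the third state covers both;
- estimate arm-specific transitions to failure from the 12- and 24-month outcomes;
- take state utilities and costs from the EQ-5D and healthcare utilization data;
- vary the failure rate after year 2 in the probabilistic sensitivity analysis, since the trial does not observe it.

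The cost is a few sentences and modest extra modelling. Failures, re-treatment, EQ-5D and resource use are already collected, so no additional patients or visits are needed. Death after year 2 would need an external mortality input.
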